## Abstract

**Objectives::**

Vascular calcification is common in patients with advanced chronic kidney disease (CKD) and
contributes to cardiovascular disease. Accumulating evidence indicates that CKD patients often
acquire subclinical vitamin K deficiency, which is associated with vascular calcification.

**Methods::**

This prospective, randomized, parallel group, multicenter trial (UMINID000011490)
will include 200 dialysis patients in an open-label, two-arm design. After baseline computed
tomography of the abdominal aorta, patients will be randomized to two groups that will either
(1) continue receiving standard care or (2) receive additional oral supplementation with
menatetrenone (45 mg/day). The treatment duration will be 24 months, and the computed
tomography scan will be repeated after 12 and 24 months. The primary endpoint is the
progression of abdominal aortic calcification, which is calculated as absolute changes based
on the Agatston score. The secondary endpoints are the decrease in bone mineral density
(measured by dual-energy X-ray absorptiometry), the biomarkers associated with vitamin K,
vitamin K intake (evaluated by the food frequency questionnaire), and the biomarkers
associated with vascular calcification.

**Conclusions::**

This study aims to confirm whether vitamin K has inhibitory effects on
calcification that can be clinically determined.

**Trial registration::**

UMINID000011490.

## Introduction

Patients with chronic kidney disease (CKD) have an extremely high risk of developing
vascular disease,^1^ and vascular calcification
is an independent risk factor for cardiovascular mortality.^2^ Thus, vascular calcification is important for the prognosis of CKD.
Clinically, vitamin D and K deficiencies are known to be risk factors for uremic vascular
calcification.^3,4^ Vitamin K comprises a group of fat-soluble vitamins that act as co-factors for
γ-glutamylcarboxylase, which activates several vitamin K-dependent proteins. Matrix Gla protein
is a vitamin K-dependent protein that is involved in inhibiting vascular calcification. The
inactive form of matrix Gla protein reflects vitamin K deficiency and has been reported to be
associated with cardiovascular events and mortality.^5^ Clinical and epidemiological studies have also indicated that long-term
treatment with a vitamin K antagonist (warfarin) increases the risk of vascular calcification in
certain individuals, possibly because of a poor vitamin K status.^6^ In CKD, vitamin K deficiency is highly prevalent and associated with
vascular calcification and cardiovascular mortality.^7^ Vitamin K2 supplemented as menatetrenone is covered by insurance owing to its
effects on osteoporosis in Japan. The aim of this clinical trial is to determine whether vitamin
K2 supplementation has an inhibitory effect on vascular calcification in addition to
osteoporosis in patients undergoing dialysis.

## Overall study aims

The primary endpoint is to determine whether vitamin K2 decreases the progression of
aortic calcification based on absolute changes as per the Agatston score.

## Trial design

This study is a multicenter, randomized, prospective, open-label, interventional
trial. Two treatments will be compared, providing a two-arm parallel group design with a total
of 200 patients.

## Inclusion criteria

Patients with the following criteria will be included in the trial: (1) Males and females ≥18 years of age(2) Patients receiving hemodialysis or peritoneal dialysis(3) Patients diagnosed with osteoporosis based on bone mineral density, blood
sampling results, or patient history.

## Exclusion criteria

(1) Life expectancy <12 months(2) Pregnancy(3) Intake of vitamin K antagonists(4) Inflammatory bowel disease(5) Hypersensitivity to vitamin K(6) History of thrombosis(7) Severe liver dysfunction.

## Treatment details

All patients will first undergo a multi-slice computed tomography (CT) scan of the
abdomen. We will use the Agatston score to quantify calcification. The Agatston score is a
semi-automated tool used to calculate a score based on the extent of arterial calcification
detected by an unenhanced CT scan. The calculation is based on the weighted density score given
to the highest attenuation value (HU) multiplied by the area of the calcification speck (130–199
HU: 1; 200–299 HU: 2; 300–399 HU: 3; and 400+ HU: 4). The calcification of the abdominal aorta
will be measured from the celiac artery branch to the inferior mesenteric artery branch. The
aorta will be regarded as a perfect circle, and only calcifications inside the circle will be
selected. Calcifications of the bifurcating arteries that branch from the abdominal aorta
(celiac, bilateral renal, superior mesenteric, testis, ovarian, and inferior mesenteric
arteries) will be excluded. Dialysis patients will be divided into two groups: a group
administered with vitamin K2 and a control group. The hemodialysis and peritoneal dialysis
patients will be randomly allocated into two groups. Half of the hemodialysis patients and half
of the peritoneal dialysis patients will be administered with vitamin K2 (the vitamin K2
administration group), whereas the other halves will receive the standard care for CKD-mineral
bone disease without vitamin K2 administration (the control group). The following seven factors
will be considered.

Hemodialysis patients: age of 70 years, sex, time on dialysis of 10 years, diabetes,
serum phosphate of 6.1 mg/dL, corrected calcium of 9.3 mg/dL, and a young adult mean
of 70% or a T score of –2.5 in dual-energy X-ray absorptiometry.

Peritoneal dialysis patients: age of 64 years, sex, time on dialysis of 4 years,
diabetes, serum phosphate of 6.1 mg/dL, corrected calcium of 9.3 mg/dL, and a young
adult mean of 70% or a T score of –2.5 in dual-energy X-ray absorptiometry.

The observation period will be 24 months. After performing abdominal CT and
dual-energy X-ray absorptiometry of bone density, an interventional study will be performed. In
the vitamin K2 administration group, menatetrenone (45 mg/day) will be orally administered
in three divided doses. Vitamin K-related biomarkers will be measured before the study and 2,
12, and 24 months later. Other calcification-related biomarkers will be measured before the
study and 24 months later. All participants will answer the Food Frequency Questionnaire before
the study. The abdominal CT and dual-energy X-ray absorptiometry of bone density will be
repeated after 1 year and 2 years.

## Ethics approval and consent to participate

This study is being conducted according to the Ethical guidelines for Clinical
Research by the Japanese Ministry of Health, Labour, and Welfare and the Helsinki Declaration.
This study was approved by the ethics committee of Fujita Health University School of Medicine
(approval number: HM20-153). The subjects will receive oral and written explanation of the study
and will provide consent to be included in the study. The trial registration number is
UMIN000011490.

## Primary endpoints

The primary endpoint is the progression of abdominal aortic calcification, which is
calculated as absolute changes based on the Agatston score in 24 months. The period from
baseline abdominal CT to the start of vitamin K2 administration will be less than 1 month.

## Secondary endpoints

We shall consider the following: (1) 
Bone mineral density: measured by
dual-energy X-ray absorptiometry(2) Biomarkers associated with vitamin K(3) Vitamin K intake: evaluated
by the Food Frequency Questionnaire(4) Biomarkers associated with vascular calcification(5) Progression of abdominal aortic calcification in 12 months.

## Justification of sample size

Sample size calculations were based on the studies by Brandenburg
et al.^8^ and Krueger
et al.^9^ Assuming the difference in the
changes in the Agatston score between the two groups was 400 and the standard deviation was 900,
we would need to enroll 80 patients per arm to detect a significant difference with a two-sided
significance level of 5% and a detection power of 80%. Correcting our total sample size of 160
by a dropout rate of 20% resulted in a total sample size of 200.

## Analysis of the primary endpoint

The primary efficacy end point is the change in abdominal aortic calcification
evaluated by the Agatston score at the 24-month visit versus the baseline visit. While we will
use the change in the abdominal aortic calcification Agatston score after 24 months as an
objective variable, the difference between the vitamin K administration and control group will
be confirmed by covariance analysis. The abdominal aortic calcification Agatston score at the
time of the baseline measurement will be added into the model as a covariate. The significance
level will be set at 5% on both sides. If a Gaussian distribution will not be confirmed in the
residuals, the change in the abdominal aortic calcification Agatston score will be examined
after logarithmic transformation.

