## Discussion

The Agatston score is a coronary artery calcium score that was proposed by Agatston
et al.^10^ in 1990. It has also been
applied for the evaluation of aortic calcification. Since the purpose of this study is to verify
whether vitamin K2 as a drug has an inhibitory effect on calcification, the progression of
abdominal aortic calcification evaluated by the Agatston score will be set as the primary
endpoint.

Few interventional studies examining the inhibitory effect of vitamin K on
calcification have been performed. Brandenburg et al. reported that the aortic valve
calcification volume score progressed by 10% in patients administered with vitamin K1 compared
with 22% in a placebo group, representing a significant vitamin K1-induced attenuation of aortic
valve calcification.^8^ Furthermore, Shea
et al. reported that phylloquinone supplementation slowed the progression of coronary
arterial calcification in healthy older adults.^11^ There have been two ongoing vitamin K interventional studies in dialysis
patients in which vitamin K1 was administered to the interventional group. To date, there has
been no vitamin K2 (menaquinone) interventional trial in dialysis patients. We believe our
present trial will contribute to finding a treatment option for vascular calcification in
dialysis patients.

Vitamin K-related markers are not routinely measured in maintenance dialysis
patients, and the treatment for vitamin K deficiency has not been standardized yet. Therefore,
we believe that not administering vitamin K supplementation for 2 years is not unethical.

The severity of vascular calcification in dialysis patients is higher than that in
healthy subjects. Jansz et al. reported that the degree of coronary calcification was not
significantly different between hemodialysis and peritoneal dialysis patients.^12^ We have assessed that similar treatment effects of
vitamin K can be evaluated in hemodialysis and peritoneal dialysis patients. As patients use
their own peritoneum, deterioration of peritoneal function hinders the continuation of
peritoneal dialysis. Therefore, the time on dialysis is shorter in peritoneal dialysis patients
than in hemodialysis patients. Patients must change the peritoneal dialysis bag by themselves,
and the mean age of the peritoneal dialysis patients is younger than that of hemodialysis
patients. For these reasons, the allocation factors differ between hemodialysis and peritoneal
dialysis.

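### Allocation uses dialysis modality and seven factors, but the primary ANCOVA names only the baseline Agatston score; if those factors predict progression, the test is conservative and some power is forgone

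*Protocol article*

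**What the plan says.** **Allocation.** The Treatment details section of the protocol article splits each modality evenly between the arms ("Half of the hemodialysis patients and half" of the peritoneal dialysis patients receive vitamin K2). It then introduces seven factors: age, sex, time on dialysis, diabetes, serum phosphate, corrected calcium and bone density. Single cut-points are given for the measured ones, and those for age and time on dialysis depend on modality. The Discussion makes the role of the seven plain: "For these reasons, the allocation factors differ between hemodialysis and peritoneal" dialysis.

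**Analysis.** The section Analysis of the primary endpoint sets out a covariance analysis of the 24-month change in Agatston score, with a two-sided 5% level and a logarithmic fallback. One covariate is named: the Agatston score, whose value at the "time of the baseline measurement will be added into the model as a covariate". Modality and the seven factors are not mentioned.

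**Sample size.** The Justification of sample size assumes that the difference in "changes in the Agatston score between the two groups was 400 and the standard deviation was 900". It arrives at 80 patients per arm for a "significance level of 5% and a detection power of 80"%, and 200 in total after allowing for dropout.

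**The concern.** When allocation balances the arms on a prognostic factor, the variation due to that factor largely drops out of the true sampling error of the treatment contrast. A model that omits the factor still counts that variation as residual. The reported standard error then exceeds the true one, confidence intervals are wider than they need be, and the test rejects less often than 5% under the null. The model as stated does not reflect the allocation as stated.

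At stake are precision and calibration in the conservative direction. Whether anything is lost depends on how well the allocation factors predict 24-month change once the baseline score is in the model.

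**Working it through.** **Inputs from the article:** difference 400, SD 900, 80 analysed per arm, two-sided 5% level, 80% power, 20% dropout.

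**Assumed:** R², the share of variance left after the baseline score that modality and the seven factors explain. The article gives no value, so 0 to 0.30 is shown. The SD of 900 is treated as the residual SD after baseline adjustment, although the article states it for the change itself.

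**Step 1: reproduce the plan.**
- n per arm = 2 × (1.960 + 0.842)² × (900/400)² ≈ 79.5, so 80.
- SE = 900 × √(2/80) = 142.3.
- Power = Φ(400/142.3 − 1.960) = 80.3%.
- Total = 160/(1 − 0.20) = 200.

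The plan's figures reproduce.

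**Step 2: omit balanced factors.** With perfect balance the baseline-only model reports SE = 142.3, while the true SE is 142.3 × √(1 − R²).
- Two-sided alpha = 2 × [1 − Φ(1.960/√(1 − R²))]
- Power, baseline-only = Φ[(400 − 1.960 × 142.3)/true SE]
- Power, adjusted = Φ[400/true SE − 1.960]

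| Assumed R² | True SE | Reported/true SE | Alpha, baseline-only | Power, baseline-only | Power, adjusted | Forgone (points) |
|---|---|---|---|---|---|---|
| 0 | 142.3 | 1.00 | 5.0% | 80.3% | 80.3% | 0 |
| 0.05 | 138.7 | 1.03 | 4.4% | 80.9% | 82.2% | 1.4 |
| 0.10 | 135.0 | 1.05 | 3.9% | 81.5% | 84.2% | 2.7 |
| 0.20 | 127.3 | 1.12 | 2.8% | 82.9% | 88.2% | 5.2 |
| 0.30 | 119.1 | 1.20 | 1.9% | 84.5% | 91.9% | 7.4 |

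Differences were taken before rounding.

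**Step 3: allow for imperfect balance.** A simulation used minimisation within modality (an assumed algorithm, since the article names none), binary factors, 160 patients and 1,500 runs per scenario. Monte Carlo error is about 0.006 for alpha and 0.010 for power.

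| R² | Alpha, baseline-only | Alpha, adjusted | Power, baseline-only | Power, adjusted |
|---|---|---|---|---|
| 0 | 0.041 | 0.044 | 0.794 | 0.783 |
| 0.10 | 0.034 | 0.049 | 0.794 | 0.822 |
| 0.20 | 0.031 | 0.047 | 0.838 | 0.889 |
| 0.30 | 0.026 | 0.050 | 0.826 | 0.907 |

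The direction agrees with Step 2. At R² = 0.30 alpha is 0.026 rather than 0.019, so imperfect balance softens the effect. At R² = 0 the eight extra terms cost 0.794 − 0.783 = 0.011, about 1 point. The average reported SE there rises only from 142.2 to 142.9.

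**The case against.** **The full covariate list may be elsewhere.** The article is condensed, the analysis plan is not shown, and naming one covariate does not exclude others. That is fair as a caution. However, the article gives the outcome, method, covariate, significance level and fallback, so it reads as a model statement, and the only model stated does not match the allocation.

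**The loss is conditional.** Nothing in the article says how strongly the factors predict change, or that they were chosen because they drive calcification. The Discussion explains only why the factors differ by modality. On modality itself, it cites a study finding no significant difference in coronary calcification between hemodialysis and peritoneal dialysis. That concerns level rather than aortic progression, but it gives no ground for assuming a large modality effect. This objection stands, and the size of the effect has to be shown as a range that includes zero.

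**Perfect balance is optimistic.** Balancing on single cut-points leaves within-category variation unbalanced, so the alpha values in Step 2 are the extreme end. This also stands.

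**Stronger readings to resist.** A reader might infer that the trial is underpowered, or that its false-positive rate is inflated. Neither follows: the baseline-only test keeps about 80% power or more at the planned assumptions, and any error is conservative. A reader might also set the adjusted power of 84.2, 88.2 or 91.9% against the planned 80.3% and infer losses of about 4 to 12 points. The baseline-only test gains from the same balance, so at those R² values the fair gap is 2.7, 5.2 or 7.4 points.

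**Conclusion.** The mismatch between the allocation and the named primary model is real, and its direction is clear. If the allocation factors predict 24-month change beyond the baseline score, the stated analysis is conservative and gives up some precision. The amount is unknown: nothing at R² = 0, about 1 to 3 points of power at R² of 0.05 to 0.10, and 5 to 7 points at 0.20 to 0.30. These figures rest on near-perfect balance, 80 analysed per arm and a residual SD of 900.

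The treatment estimate is not biased and the sample size is not wrong. This is a free or cheap improvement, not a fault that threatens validity.

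**What to change.** Before outcome data are examined, specify the primary ANCOVA as 24-month change on arm, baseline Agatston score, dialysis modality and the seven allocation factors. State the form in which each factor enters. Using the classes applied at allocation, with their modality-specific cut-points, matches the design directly. Keep the baseline-only ANCOVA as a sensitivity analysis.

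With one term per factor, the model has 11 parameters (intercept, arm, baseline score, modality and seven factors) for about 200 × 0.80 = 160 completers. The change is one of wording, and the factors are already needed for allocation. The statistical cost is eight degrees of freedom, at most about 1 point of power if none of the factors is prognostic.

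Timing matters because the trial is open-label and the article reports 110 patients already registered. Covariates added after outcomes are seen would look data-driven.

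### The fallback for the primary analysis logs the 24-month change, which has no logarithm at zero or below, and gives no rule for such patients

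*Protocol article*

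**What the plan says.** The Primary endpoints section defines progression as "calculated as absolute changes based on the Agatston score in 24 months". The section Analysis of the primary endpoint will "use the change in the abdominal aortic calcification Agatston score after 24 months as an" outcome in a covariance analysis, with the baseline score as covariate and a two-sided 5% level.

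The same section adds a conditional step for residuals that are not confirmed to be Gaussian: "residuals, the change in the abdominal aortic calcification Agatston score will be examined" "after logarithmic transformation". It gives no added constant, no ratio form and no handling of values at or below zero. It also does not say how normality is judged.

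The Justification of sample size works on the raw scale. It assumes that the difference in "changes in the Agatston score between the two groups was 400 and the standard deviation was 900", and arrives at 80 per arm for 80% power at the two-sided 5% level.

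**The concern.** An absolute change can be negative or zero. Scan-to-scan variability can produce a small fall, treatment may do the same, and a patient without calcification at either scan has a change of exactly zero. The inclusion and exclusion criteria set no minimum calcification score, so such patients can be enrolled. For all of them the logarithm of the change does not exist, and the stated step cannot be carried out.

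The analyst then has two ways out, neither specified:

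- **Delete these patients.** They have the best outcomes, so this is selection on the outcome after randomisation. If K2 slows progression, it removes more K2 than control patients and pulls the comparison towards no effect.
- **Add a constant.** The result then depends on a number chosen once the data are known, in an open-label trial.

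The switch itself is also decided by the outcome data. It moves the primary test from a difference in Agatston units, which the trial was sized to detect, to a difference in mean log change, for which no planning figure exists.

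**Working it through.** **1. The plan's own figure.** Inputs from Justification of sample size: difference 400, SD 900, two-sided 5%, power 80%.

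n per arm = 2 × (1.960 + 0.842)² × (900/400)² = 2 × 7.849 × 5.0625 = 79.5, so 80.

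Total with 20% dropout = 160 / 0.8 = 200. Both figures reproduce, so the sample size is sound for the raw-scale analysis.

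**2. Share of changes at or below zero.** The article gives no mean change, so the control mean is an assumption, shown as a range. The K2 mean is set 400 lower. With normal changes, the share at or below zero is Φ(−mean/900). For example, at a control mean of 600 it is Φ(−0.667) = 25% in controls and Φ(−0.222) = 41% under K2.

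The mean among patients with a positive change is mean + 900 × φ(mean/900)/Φ(mean/900). At 600 this gives 985 for control and 796 for K2, a difference of 189.

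The power column is simulated (3000 runs, 80 per arm, t-test of log change without the baseline covariate, values at or below zero deleted). Raw-scale power in the same runs is 80%.

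| Control / K2 mean (assumed) | Share ≤ 0, control vs K2 | Expected number of 80 | Raw difference among those left | Power, log with deletion |
|---|---|---|---|---|
| 600 / 200 | 25% vs 41% | 20 vs 33 | 189 | 28% |
| 1000 / 600 | 13% vs 25% | 11 vs 20 | 239 | 37% |
| 1500 / 1100 | 5% vs 11% | 4 vs 9 | 303 | 53% |
| 2000 / 1600 | 1% vs 4% | 1 vs 3 | 354 | 63% |

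At 2000 / 1600 few patients are lost but power still falls, because the logarithm turns small positive changes into extreme low values. Normal changes are also the case in which the fallback should seldom be triggered, so these powers are illustrative only.

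**3. Skewed changes, where the fallback would be triggered.** All models below are assumptions.

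- *Shifted gamma, shape 2, SD 900, difference 400.* Shares ≤ 0 are 29% vs 50% at control mean 600, 7% vs 29% at 1000, and 0% vs 3% at 1500. Power of log change with deletion is 7%, 19% and 96%; raw-scale power is 79%.
- *Lognormal progression plus scan noise of SD 100, equal coefficient of variation in both arms, pooled SD about 900.* At means 733 / 333, shares are 4% vs 11% and log power is 92% against 91% raw. At 1000 / 600, shares are 1% vs 3% and log power is 90% against 86% raw.
- *Gamma progression with the same noise and equal coefficient of variation.* Log power is 61–62% against 83–86% raw.

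**4. Adding a constant.** In the shifted-gamma case at control mean 1000, shifting all values above zero by a constant taken from the data gave 96–99% power, against about 20% with deletion and about 80% on the raw scale. The same protocol sentence therefore allows very different tests of the same data.

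**The case against.** The strongest objections, and what stands of each:

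- **The article never says that patients will be dropped.** This is correct. A reader might infer that the plan deletes patients without progression, but no complete-case rule is stated. Deletion is what happens by default when a logarithm is taken of such values. The other route, a constant, is equally unspecified.
- **A milder reading is possible:** log the scores, then take the change. The sentence names the change as the variable transformed, so this is not what it says. It would also turn an absolute endpoint into a relative one, and would still need a rule for zero scores.
- **The handling of zeros may be in a full protocol or SAP.** It may. But the article does not leave the fallback open. It fixes one that cannot be computed for every possible value of the endpoint.
- **The step is conditional.** This is true. The first-line analysis, raw-scale ANCOVA with baseline, is sound, and the defect appears only if the switch is made.
- **A large loss of power is not shown.** This also stands. The lowest power figures come from a shifted gamma whose lower limit is the mean minus 2 × 900/√2 = 1273. At a K2 mean of 600 it allows falls of up to 673 Agatston units, which nothing in the article supports. The lognormal model shows no loss. The 22% and 10% progression figures in the Discussion do not settle the mean, since they are aortic valve volume scores under vitamin K1.
- **The K2 excess is conditional.** With no treatment effect, expected losses are equal in the two arms. The harm from deletion is then attenuation and lost power, not a false claim of benefit.

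**Conclusion.** The point holds as a specification error in the primary analysis: the stated fallback is undefined for values that the endpoint allows, it is triggered by the outcome data, and it leaves the scale on which the trial was sized.

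Its size cannot be determined from the article. With normal changes, SD 900 and a difference of 400, between 25% vs 41% (control mean 600) and 1% vs 4% (control mean 2000) of control and K2 patients would have no logarithm. Power after deletion runs from 7% to above raw-scale power, depending on the mean and shape assumed.

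A reader might infer that the trial will lose most of its power, or is biased against K2. The documents support neither: they do not prescribe deletion, they give no mean change, and the excess in the K2 arm exists only if K2 works. The case for acting is that an undefined rule governs the primary test and can be replaced at almost no cost.

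**What to change.** Remove the log-of-change fallback. Keep one primary analysis for all patients: ANCOVA of the 24-month change on the raw scale with baseline Agatston score as covariate, with heteroscedasticity-robust (HC3) or bootstrap confidence limits if residuals are non-normal. Name the method in advance. This matches the endpoint definition and the sample size.

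If a log-scale analysis is wanted, pre-specify it as a sensitivity analysis on the scores: log(24-month score + 1) on log(baseline score + 1) and arm, reported as a ratio. The constant is then fixed beforehand and zero scores stay in.

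The cost is one paragraph in the protocol or SAP before database lock, with no extra data and no change to the sample size. The small downside is that raw-scale ANCOVA may be less efficient than a log-scale analysis if changes are strongly skewed and almost all positive.
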